**Table S1 - Organ failure descriptors**

| **Upper airway** positive for inclusion and allocation to primary or secondary organ failure by critical care specialists:   - Stridor - Altered voice - Tongue/oropharyngeal swelling - Obvious laryngeal swelling at 1^st^ laryngoscopy - Gross macroscopic laryngeal swelling at autopsy - Recorded as Negative/No Upper airway involvement if only microscopic/minor laryngeal swelling at autopsy.   Notes: Criteria developed on expert consensus with consideration of upper respiratory descriptors in published grading systems. Laryngeal swelling may occur after multiple laryngoscopy attempts^1^ – first laryngoscopy and autopsy findings have been qualified to take this confounding element into consideration. Number of laryngoscopy attempts is recorded during data extraction. |
| --- |
| **Bronchospasm** positive for inclusion and allocation to primary or secondary organ failure by critical care specialists:   - Persistent cough - Wheeze - Chest tightness with history of asthma - Shortness of breath with history of asthma - Cyanosis or hypoxia <93% with history of asthma (excluding isolated airway obstruction) - Cyanosis hypoxia <93% without documented or clinical hypotension - Increased work of breathing (excluding isolated upper airway obstruction) - Patient’s usual asthma symptoms - Bronchodilator use during episode - High peak inspiratory pressure in intubated patient (subjective or greater than 30cm H2O) - Difficult to ventilate - Upsloping CO2 trace or obstructive airway pattern   Notes: Criteria developed on expert consensus with consideration of lower respiratory descriptors in published grading systems. Airway obstruction, bronchospasm and cardiovascular symptoms can overlap. Criteria have been developed to exclude overwhelming upper airway obstruction in the absence of obvious bronchospasm. Chest tightness and shortness of breath may be a manifestation of cardiovascular involvement if not associated with asthma symptoms or pre-existing asthma increasing the pre-assessment probability of symptom origin. Dyspnoea, cyanosis and hypoxia can overlap with cardiovascular compromise.^2, 3^ Brown reported 12 % of hypotensive patients developed *dyspnoea* where 100% of hypoxic patients had either dyspnoea or wheeze. In the same study 10% of wheezy patients had hypotension. |
| **Cardiovascular** involvement for inclusion and allocation to primary or secondary organ failure by critical care specialists:   - Hypotension without *severe* respiratory symptoms - Dizziness or feeling faint without *severe* respiratory symptoms - Dyspnoea without severe respiratory symptoms/increase work of breathing. - Postural dizziness without severe respiratory symptoms - Sweating and nausea without severe respiratory symptoms - Tachycardia meeting red ViCTOR^4^ criteria prior to adrenaline and without severe respiratory symptoms - Requiring ongoing vasopressor support even if respiratory symptoms present - Negative/not for inclusion if cardiac arrest only manifestation recorded. |

**Study Protocol**

**Background**

Study of fatal anaphylaxis reactions gives clinicians important information to help avoid this catastrophic outcome in the future, for both patients known to be at risk of anaphylaxis and those who unexpectedly experience a reaction.

Anaphylaxis is an acute-onset, potentially fatal systemic allergic reaction that can affect multiple organs either simultaneously or singularly in isolation. It is usually triggered by an agent such as an insect sting, food, or medication, through a mechanism involving IgE and the high-affinity IgE receptor on mast cells or basophils^5^. Less commonly, it is triggered through other immunologic mechanisms, or through nonimmunologic mechanisms. Anaphylaxis is distinguished from milder allergic reactions when a person’s airway, breathing or circulation become affected^6^. Death occurs when organ failure occurs and is not supported with treatment in the rapid time frame that anaphylaxis evolves within.

Anaphylaxis itself has a spectrum of severity and grading systems exist to quantify the severity of reaction^3, 7-9^. Most cases can be treated with one or two doses of intramuscular adrenaline but approximately 3% of cases need more than two doses^10^. In the most severe reactions, cardiorespiratory arrests occur due to organ failure. These episodes are rare but are an important cause of unexpected and potentially preventable death and disability in all ages^11^. The three main mechanisms of rapid organ failure in anaphylaxis are upper airway oedema, lower airway obstruction principally from bronchospasm, and cardiovascular failure^12^. Beyond treatment with adrenaline, these different types of organ failure require different emergency medical interventions for the patient to survive. Understanding the frequency of each organ system failure in anaphylaxis, including in clinical subgroups, can help inform treatment recommendations to target time critical organ support for these patients.

*Types of organ failure in anaphylaxis*

Anaphylaxis symptoms occur principally through chemical mediators released during mast cell degranulation triggered by cross linking IgE on the mast cell surface by an antigen^13^. A number of chemical mediators are released that include histamine, platelet activating factor, interleukins and leukotrienes. Multiple factors will influence which organs are affected most during an anaphylaxis episode although exact reasons are not well understood. Concentration of antigen and mast cells in a tissue and underlying organ diseases are likely to be significant factors.

*Upper airway oedema*

Mast cells are prevalent throughout the body but have high concentrations in the airway. Histamine and other inflammatory mediators released during anaphylaxis promote vascular permeability and cause swelling. Severe swelling of the tongue, pharynx and larynx can contribute to death through upper airway asphyxia or through impeding delivery of critical medical interventions such as endotracheal intubation which becomes more difficult due to the swelling. Symptoms of airway failure are uncontroversial and hypoxia and cyanosis are late clinical signs prior to death.

*Bronchioles – Bronchospasm – Lower Respiratory Obstruction*

Bronchioles have the highest concentration of mast cells in the airways.^13^ Anaphylaxis inflammatory mediators cause bronchial smooth muscle to contract, promote mucous production and contribute to mucosal wall swelling all causing obstructive airflow limitation. The subsequent increased resistance causes acute hypoxic respiratory failure which can be rapid.

*Cardiovascular*

Inflammatory mediators in anaphylaxis produce vascular vasodilation. Increased vascular permeability causes oedema of body tissues and can cause depletion of intravascular volume contributing to hypotension. Varying degrees of hypotension through this mechanism are described by the widely used Ring and Messner grading scale.

Mast cells also exist in cardiac muscle and their chemical mediators may cause decreased cardiac contractility and may manifest with ECG changes. Mast cells also be part of inflammation in coronary artery atheromatous plaques^14^. Rupture of these plaques during the physiological insult of anaphylaxis has also been reported but may or may not be unique to anaphylaxis.

*Organ failure interrelations and overlap of symptoms*

Vital organ systems do not operate in isolation and are connected in structure and function. There is overlap of symptoms where multiple organ involvement contributes to a clinical endpoint such as hypoxia or hypotension. Cessation of blood flow/absence of blood pressure is the final common pathway but may be caused by hypoxia or primary cardiovascular system compromise or a combination. For example, bronchospasm induced severe hypoxia leads to a bradycardic response and decreased cardiac contractility causing cardiac arrest. Bronchospasm can also induce high intrathoracic pressures decreasing venous return to the heart and cause low blood pressure. At the same time that these respiratory processes are occurring, anaphylaxis mediators may cause systemic vasodilation leading to potentiation of low blood pressure from respiratory causes. A diagram showing interdependencies from an anaesthesia perspective have previously been published.^15^

Similarly reduced cardiac output can result in peripheral hypoxaemia and peripheral cyanosis if severe. It is rare however for central cyanosis to be caused by reduced cardiac output. Of 38 anaphylaxis patients with hypoxia (SaO2 <93%) or cyanosis reported by Brown ^2^, 25 had wheeze, five were deemed to have no wheeze and eight could not be put into either group. Importantly only two were deemed to be due to hypotension alone reinforcing the rarity of cyanosis being caused by the heart and peripheral circulation component of anaphylaxis.

Using a combination of clinical experience and published data, it is feasible to allocate presence or absence of each organ failure type if sufficient clinical details are available. Where there are multiple organs involved it is feasible to record the presence of each organ involved and allocate which is the most significant contributor to death.

*Previously published case series regarding organ failure*

A systematic review studying the type of organ failure in published cases of anaphylaxis identified 14 case series reporting a total of 533 cases. Reporting of organ systems failure leading to death and disability was generally low quality with only one author reporting it as an explicit outcome and this series did not describe the methodology for allocation.

Most series reported respiratory symptoms as a composite of airway oedema and bronchospasm and only three authors separated respiratory components. The predominant organ systems failure or sequence of organ failure was only reported by two authors. Cardiovascular failure ranged from 12% to 100%. Respiratory failure was present in most cases ranging from 53% to 100%. Food related fatalities were children and young adults who died predominantly from respiratory failure with a high frequency of bronchospasm reported (75%). Venom series were older with a very high frequency of cardiovascular collapse (59% to 81%) and lower frequency of respiratory involvement (19% to 53%) which was predominantly upper airway failure when present. Drug related fatalities had high frequencies of both cardiovascular (47% to 100%) and respiratory (60% to 74%) failure.

*Australian National Coronial Information System*

In Australia each state and territory jurisdiction legislates that any unexpected death is reported to the state Coroner, including those that occur in healthcare. The coroner’s role is to establish the cause of death and circumstances through collation of eye witness statements and medical records as well as autopsy. For each reported death the coroner produces formal written findings. The National Coronial Information System contains all deaths reported to state coroners and includes documents that include the formal findings, the police report containing any eyewitness accounts of events surrounding the death, toxicology reports and formal autopsy findings with case synthesis.

Anaphylaxis deaths are all unexpected and are thus reported to state coroners and contained within the NCIS. However, there are some cases where coronial notification is not made and a death certificate is written by medical practitioners without coronial involvement. This occurs where circumstances and cause of death are clear and the requirement for notification is interpreted differently by individual medical practitioners. In a previous anaphylaxis study by Mullins et al comparing national death certificates through the Australian Bureau of statistics and NCIS case reports between 2000 and 2013, 223 out of 298 were recorded in the NCIS.^16^ It is not possible to determine which cases are not reported to state coroners. Despite this missing data, NCIS cases can be considered to be representative of a whole population.

*Cohort Studies*

Cohort studies form a suitable study design to assess associations between multiple exposures on the one hand and multiple outcomes on the other hand. They are especially appropriate to study rare exposures or exposures for which randomization is not possible for practical or ethical reasons^17^, both of which are the case in studying anaphylaxis fatalities. This study will be reported in line with the The Strengthening the Reporting of Observational Studies in Epidemiology (STROBE) statement: guidelines for reporting observational studies^18^.

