**Methodology**

*Objective*

To examine differences in organ failure that develop in patients who have fatal anaphylaxis after being exposed to different allergen trigger categories.

*Primary Question*

Is allergen exposure category associated with the type of organ failure that subsequently develops in fatal anaphylaxis?

*Design, Setting and Participants*

This is a population based retrospective analysis of consecutive anaphylaxis deaths of all ages in Australia between 1^st^ January 2003 and 31^st^ December 2022.

*Outcome*

Development of primary organ failure being either due to: Upper airway oedema, Bronchospasm (lower respiratory obstruction), Cardiovascular.

*Exposure*

Patient allergen exposure to one of 4 categories of allergens: Drug; Insect; Food; and Radiology Contrast.

*Covariates*

Covariates collected are Age, pre-existing history of asthma, pre-existing atopic disease, previously allergic to allergen, American Society of Anaesthesia Physical Status score, use of antihypertensives.

*Other variables*

A broad range of variables have been defined (Table 1 and 2) prior to data collection and may be used as covariates – see below

*Ethical Approval*

Approval was obtained from the University of Melbourne Research Ethic Committee, the Victorian Department of Justice Human Research Ethics Committees and the Coroners Court of Victoria Research Committee.

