## Secondary Objectives

To compare the following outcomes by patient allergen exposure:

1. Time to symptoms from allergen exposure.
2. Time from symptom onset to severe symptoms.
3. Time from severe symptoms to cardiorespiratory arrest.
4. Time from arrest to death.
5. Whether the patient required tracheal intubation.
   1. If required tracheal intubation, the timing of tracheal intubation.
   2. Time to tracheal intubation from cardiorespiratory arrest.
6. Whether the patient experienced vomiting or aspiration.
7. Whether the patient received cardioversion (defined as no shocks vs at least one shock).
8. Change in posture.
9. Frequency of deaths per year over time (by allergen exposure and by age group).

To compare primary organ failure by the following complications:

1. Difficult airway (FONA, failed intubation, or 3 or more attempts at intubation)
2. FONA (front of neck access)
3. Vomiting or aspiration
4. Pneumothorax (dichotomised to none OR one+/- both sides)
5. Cardioversion

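### The plan calls coroner-recorded deaths representative although its own source found about a quarter of anaphylaxis deaths missing from the register; national counts and trends are not supported, and odds-ratio bias is possible but not shown

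*Combined protocol and SAP*

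**What the plan says.** The Background subsection on the Australian National Coronial Information System makes five statements in one paragraph:

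- Complete capture: "Anaphylaxis deaths are all unexpected and are thus reported to state coroners and contained within the NCIS".
- Some deaths are nevertheless certified by a doctor without the coroner: "This occurs where circumstances and cause of death are clear and the requirement for notification is interpreted differently by individual medical practitioners".
- A previous study compared national death certificates with "NCIS case reports between 2000 and 2013", and "223 out of 298 were recorded in the NCIS".
- The gap cannot be characterised: "It is not possible to determine which cases are not reported to state coroners".
- The conclusion: "Despite this missing data, NCIS cases can be considered to be representative of a whole population".

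Methodology (Design, Setting and Participants) carries the conclusion forward: "This is a population based retrospective analysis of consecutive anaphylaxis deaths of all ages in Australia", for 2003 to 2022. The SAP's Study Population section repeats this, and the study title speaks of an Australian population cohort. SAP Secondary Objectives item 9 and section 6.1 plan yearly death frequencies by allergen and by age group, with incidence rate ratios from Poisson regression and an exposure-by-time interaction. The SAP's missing-data provisions (Handling of Missing Data, and the sensitivity analyses for primary and secondary outcomes) deal with missing values among included cases.

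**The concern.** The first and third statements contradict each other, and the last does not follow from the fourth. Not knowing which deaths are absent is a reason to withhold a claim of representativeness. No comparison of captured and uncaptured deaths is offered.

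The stated reason for non-notification is at least partly systematic, because clarity of circumstances and cause is a feature of the death itself.

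Three things are at stake:

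- Yearly counts describe coroner-notified deaths and understate Australian anaphylaxis deaths.
- The allergen mix is distorted if notification varies by allergen, and a time trend is distorted if notification changes over the years. A change over time that differs by allergen would feed straight into the planned interaction.
- The primary odds ratios could be affected, under a narrower condition set out in the working.

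No planned analysis examines any of these.

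**Working it through.** **1. Capture.** Input: 223 of 298 (Background). 223/298 = 74.8% captured; 75/298 = 25.2% missed (exact 95% interval 20.3% to 30.5%).

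**2. Unseen deaths.** Table S4, vomiting row, gives drug 179, food 64, insect 63 and contrast 45, total 351. This is a row denominator, not a stated cohort size. Assuming 2000-2013 capture held in 2003-2022: 351/0.748 = 469, so about 469 - 351 = 118 unseen.

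**3. Trend.** If true deaths were constant and capture drifted from 0.70 to 0.80 (assumed), the apparent rise would be 0.80/0.70 = 1.14-fold. From 0.65 to 0.85 it would be 1.31-fold.

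**4. The plan's odds ratios reproduced.** From Tables S2a and S2b:

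- Bronchospasm, Insect v Drug: (9 × 47)/(28 × 68) = 0.222.
- Bronchospasm, Food v Drug: (55 × 47)/(3 × 68) = 12.672.
- Cardiovascular, Insect v Drug: (21 × 75)/(16 × 40) = 2.461.

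All match the printed unadjusted values.

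**5. When selection biases an odds ratio.** Let s be the notification probability, with D for drug, E for the other allergen, 1 for the named organ failure and 0 for any other. Dividing each cell by its s gives

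corrected OR = observed OR × (s_D1/s_D0) ÷ (s_E1/s_E0).

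If s depends on allergen only, both ratios are 1. If it depends on organ failure only, they cancel. The OR moves only when notification depends on both jointly.

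**6. Assumed joint selection.** Notification differs by mechanism within drug deaths only, and comparator notification does not vary by mechanism (0.748 throughout). Each range covers both directions of the split.

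| Unadjusted contrast | Observed | 0.65 v 0.85 | 0.55 v 0.95 |
|---|---|---|---|
| Bronchospasm, Insect v Drug | 0.222 | 0.170 to 0.291 | 0.129 to 0.384 |
| Bronchospasm, Food v Drug | 12.672 | 9.69 to 16.57 | 7.34 to 21.89 |
| Bronchospasm, Contrast v Drug | 0.642 | 0.491 to 0.839 | 0.372 to 1.109 |
| Cardiovascular, Insect v Drug | 2.461 | 1.882 to 3.218 | 1.425 to 4.251 |

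**7. Tipping points.** Under the same condition, the ratio of notification probabilities within drug deaths that brings a limit or estimate to 1 is that value, or its reciprocal when it is below 1. For an OR above 1, drug deaths with the named organ failure must be the less often notified; for an OR below 1, the more often.

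| Unadjusted contrast | OR (95% CI) | Nearer limit reaches 1 at | Estimate reaches 1 at |
|---|---|---|---|
| Bronchospasm, Insect v Drug | 0.222 (0.096 to 0.514) | 1/0.514 = 1.95 | 1/0.222 = 4.50 |
| Bronchospasm, Food v Drug | 12.672 (3.741 to 42.924) | 3.74 | 12.67 |
| Bronchospasm, Contrast v Drug | 0.642 (0.277 to 1.489) | interval already includes 1 | 1/0.642 = 1.56 |
| Cardiovascular, Insect v Drug | 2.461 (1.156 to 5.237) | 1.16 | 2.46 |
| Upper airway, Insect v Drug | 3.600 (1.171 to 11.067) | 1.17 | 3.60 |

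**8. Are these ratios compatible with 75% capture?** For cardiovascular Insect v Drug, 80% v 69% gives 0.80/0.69 = 1.16. Overall drug capture is then 115/(75/0.80 + 40/0.69) = 75.8%, in line with the cited figure. Bringing the estimate to 1 would need drug capture no higher than 115/(40 × 2.461 + 75) = 66%. For bronchospasm Insect v Drug the ceiling is 115/(68 + 47 × 4.50) = 41%.

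**The case against.** The plan discloses the under-capture, its size and the fact that the absent deaths cannot be identified. It defines cases operationally by an NCIS search, commits to STROBE reporting, labels all secondary objectives descriptive, and plans no national rate with a population denominator. On this view only a background sentence is too strong. The disclosure deserves credit, but it does not support the conclusion drawn from it, and a descriptive count still needs the right population label.

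Three stronger readings are tempting, and the documents support none of them.

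- A reader might infer that the odds ratios are biased. Nothing in the documents shows notification depending on allergen and organ failure jointly, and the large bronchospasm contrasts (Food v Drug, Insect v Drug) keep their direction under every split tried.
- A reader might infer that the absent deaths are mainly drug and contrast deaths, or those with an evident mechanism. The plan gives no such split. It also cites differing interpretation by practitioners, notes that the reporting duty extends to deaths in healthcare, and a clear cause may mean only that anaphylaxis was clear.
- A reader might take 25% as the loss in this cohort. It comes from 2000-2013, and no change in notification practice is reported.

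It is also fair to say that the notification grid has no source in the documents and that the check above is unadjusted, whereas the primary model adjusts for age.

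**Conclusion.** The point holds for the population claim. The plan asserts representativeness that its own figures do not support: 25.2% of deaths were absent in the cited source, for a partly systematic reason, and they cannot be identified. National yearly counts are understated, by about 118 on 351 categorised deaths if the older capture rate applies. Distortion of allergen mix or trend is conditional on notification varying by allergen or over time.

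For the primary odds ratios, bias is possible and untested, not demonstrated. Sensitivity differs by contrast. The lower limits for cardiovascular and upper-airway Insect v Drug reach 1 at ratios of about 1.16 and 1.17, whereas moving the bronchospasm Insect v Drug or Food v Drug estimates to 1 needs ratios of 4.50 and 12.67. All of these figures are unadjusted, rest on assumed notification probabilities, and require that comparator notification does not vary by mechanism. Scaling a confidence limit also treats the notification ratio as known.

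**What to change.** 1. In the Background, delete the representativeness sentence and the sentence placing all anaphylaxis deaths in the NCIS. Keep the 223 of 298 figure and state the limitation.
2. In the Background, in Methodology (Design, Setting and Participants) and in the SAP's Study Population section, define the population as coroner-notified anaphylaxis deaths.
3. In SAP Secondary Objectives item 9 and section 6.1, report frequencies and rate ratios as those of coroner-notified deaths, without national inference.
4. Add one short tipping-point table for the primary contrasts. For each, give the notification ratio at which the nearer confidence limit and the estimate reach 1. Label the notification probabilities as assumptions and state the condition on the comparator. Either apply the weights in the age-adjusted model or label the table as unadjusted.

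The cost is a narrower population claim, a few wording changes and a little more analysis. An unadjusted table needs only the existing counts; an age-adjusted one means refitting the model with weights. No new data are required.
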